### Sample size

The PASS software version 15.0.5 (NCSS, LLC, Kaysville, UT, USA) was used to estimate the sample size. We assumed that the clinical pregnancy rate is 65% in the letrozole ovulation regimen group and 40.8% in the programmed regimen group based on past retrospective investigations [6]. To detect an absolute difference in CPRs, the study will involve 66 women in each group with a power of 80% and an alpha error of 0.05. Considering a 10% follow-up drop-out rate, our target sample size will be 148 women.

To minimize the loss of follow-up, we optimize our strategies of follow-up, including text messaging reminders to patients’ mobile phones the day before scheduled appointments, reducing the number of clinic visits if possible, and regular review of patients with missed appointments to allow early contact and intervention.

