### Outcome and outcome assessments

The primary outcome is the clinical pregnancy rate, defined as the ratio of the clinical pregnancy (intrauterine gestation sac) number to the number of patients who received embryo transfer. The secondary outcomes include abortion rate, live birth rate, birth weight, pregnancy and perinatal complication, and neonatal complication.

Two weeks following embryo transfer, serum β-HCG is tested; a result of ≥ 10 IU/L indicates biochemical pregnancy. The patients who are biochemically pregnant will keep taking medications for luteal support. The existence of a gestational sac within the uterine cavity is referred to as clinical pregnancy. When the embryo implants anywhere other than the uterine cavity, it is referred to as an ectopic pregnancy. Around 5 weeks following embryo transfer, a transvaginal ultrasound is carried out to confirm clinical pregnancy. When a viable fetus with a fetal heartbeat is detected by ultrasound around 10 weeks following embryo transfer, it is considered to be an ongoing pregnancy.

Abortion rate is defined as the ratio of the number of nonviable pregnancies before 28 weeks of gestation to the number of clinical pregnancies. Abortion before 12 weeks of pregnancy is called early abortion while after 12 weeks of pregnancy is called late abortion. Live birth rate refers to the ratio of the number of normal fetuses delivered at 28 weeks or later of gestation to the number of patients who received embryo transfer. Preterm birth occurs between 28 and 37 weeks of gestation. A birth at 37 weeks or later is called a full-term birth. The congenital malformations are diagnosed after birth.

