### Data analysis

All the generated data in the trial will be analysed by blinded independent biostatisticians. The primary analysis will be performed according to the intention-to-treat (ITT) principle. The Statistical Package for the Social Sciences (version 24.0; SPSS Inc., USA) will be used for all analyses. All tests will be two-tailed, and a *P* value < 0.05 is considered to be statistically significant. The primary outcome, clinical pregnancy rate, will be analysed using the chi-square test. The secondary outcomes such as abortion rate, live birth rate, and some complications will be analysed using the chi-square test or Fisher’s exact test for expected frequencies less than 5. The other parameters will be analysed and compared according to the following methods. The Shapiro-Wilk test will be used to test the normal distribution of continuous variables. For normally distributed data, we will use Student’s *t*-test to examine the differences between groups; for non-normally distributed data, we will use the Wilcoxon rank-sum test. Continuous variables will be represented as means ± standard deviations. Categorical variables will be described as frequencies or percentages, and the chi-square test or Fisher’s exact test is used to examine the differences between groups.

We will perform a secondary per-protocol analysis according to the actual treatment that subjects received who comply with the protocol. The data analysis methods are as above.

Missing data will be treated as missing at random and will be imputed using the last observation carried forward method. For the missing values, a sensitivity analysis will be done under the hypothesis of the worst and the best outcomes for each missing individual. Therefore, all secondary per-protocol analysis outcomes will be considered exploratory. All statistical analyses will be done using the statistical package SPSS (version 24.0; SPSS Inc., USA).

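### Missing pregnancy outcomes are to be imputed by last observation carried forward, which does not follow from the stated missing-at-random assumption and does not suit outcomes each assessed once; the worst/best sensitivity analysis also needs its direction stated

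*Protocol article*

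**What the plan says.** The Data analysis section of the protocol article gives one rule for incomplete data and limits it to no outcome: "Missing data will be treated as missing at random and will be imputed using the last observation carried forward method". It adds that "a sensitivity analysis will be done under the hypothesis of the worst and the best outcomes for each missing individual". The same section states that "The primary analysis will be performed according to the intention-to-treat (ITT) principle", and, for the test, "The primary outcome, clinical pregnancy rate, will be analysed using the chi-square test".

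Outcome and outcome assessments describes a sequence of distinct events: serum β-HCG two weeks after transfer; then, at about 5 weeks, "a transvaginal ultrasound is carried out to confirm clinical pregnancy"; then a fetal heartbeat at about 10 weeks; then delivery at 28 weeks of gestation or later. Clinical pregnancy and live birth are both expressed per woman who received a transfer, and abortion per clinical pregnancy. Under Follow-up plan, what happens after clinical pregnancy is collected from records or by telephone near 13 and 29 weeks of gestation, at delivery, and 6 weeks after delivery.

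**The concern.** Two things do not fit together.

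First, the assumption and the method. Under MAR, a missing outcome can be predicted from what was observed, which leads to multiple imputation or a likelihood model. LOCF assumes instead that nothing changes after the last contact, and it treats the filled-in value as known. Assuming MAR does not make LOCF valid.

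Second, the method and the outcomes. Each outcome is a single event, so there is no earlier reading of the same variable to carry. If the rule is applied at all, an earlier stage has to stand in for a later one: a positive β-HCG for a clinical pregnancy, or a sac for a live birth with no abortion. The stages are kept apart because pregnancies are lost between them. Carrying a positive stage forward can therefore only raise the later success rate and lower the abortion rate. The main exposure is live birth and abortion, where follow-up is long and remote. For clinical pregnancy the only open interval is from β-HCG to the scan.

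The sensitivity analysis is the natural safeguard, but its wording leaves open whether both arms move in the same direction or in opposite directions. These are very different tests of robustness.

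**Working it through.** **Inputs from the document.** Sample size section: "the clinical pregnancy rate is 65% in the letrozole ovulation regimen group and 40.8% in the programmed regimen group"; "the study will involve 66 women in each group with a power of 80% and an alpha error of 0.05"; 10% drop-out; 148 women in total. Data analysis section: "All tests will be two-tailed". Pregnancy-loss rates, and how missingness splits between stages and arms, are not given. Those used below are assumptions.

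**1. The plan's own figure.** Two proportions, pooled variance, no continuity correction, mean rate (0.65 + 0.408)/2 = 0.529:

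n = [1.96·√(2·0.529·0.471) + 0.842·√(0.65·0.35 + 0.408·0.592)]² / 0.242² = 65.6, so 66 per group (power 80.2%). Then 66/0.9 = 73.3, so 74 per group and 148 in total. The stated figures reproduce.

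**2. LOCF and live birth.** Let p be the clinical pregnancy rate, m the share of clinical pregnancies lost before birth, and x the share of clinically pregnant women not seen again after the scan. The true rate is p(1 − m). Under LOCF it becomes p[(1 − x)(1 − m) + x], an excess of p·x·m. With x = 0.10 and m assumed to be 0.10 to 0.25:
- letrozole: 0.65·0.10·m = 0.7 to 1.6 points (at m = 0.20, 52.0% becomes 53.3%);
- programmed: 0.408·0.10·m = 0.4 to 1.0 points (at m = 0.20, 32.6% becomes 33.5%);
- difference between arms: 0.242·0.10·m = 0.2 to 0.6 points.

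The abortion rate per clinical pregnancy falls from m to m(1 − x), for example from 20% to 18%.

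**3. LOCF and clinical pregnancy.** Let b be the assumed share of β-HCG positives without a later sac. Carrying β-HCG forward for 10% of women gives 0.9p + 0.1p/(1 − b). For b from 0.05 to 0.20, letrozole goes from 65.0% to 65.3–66.6%, programmed from 40.8% to 41.0–41.8%, and the difference from 24.2 to 24.3–24.8 points.

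**4. Unequal missingness with no true effect.** Assume p = 0.55 in both arms and m from 0.10 to 0.30. The spurious live-birth difference is p·m·(x₁ − x₂):
- 15% against 5% missing: 0.55·m·0.10 = 0.6 to 1.7 points;
- 20% against 0% missing: 0.55·m·0.20 = 1.1 to 3.3 points.

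**5. Two readings of the worst/best analysis.** Take 74 per arm, 7 missing in each, and observed results near the planning rates: 44/67 against 27/67 (25.4 points, P = 0.003). The P values are from the chi-square test without continuity correction.

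| Missing women set to | Letrozole | Programmed | Difference | P |
|---|---|---|---|---|
| failure in both arms | 44/74 | 27/74 | +23.0 | 0.005 |
| success in both arms | 51/74 | 34/74 | +23.0 | 0.005 |
| failure letrozole, success programmed | 44/74 | 34/74 | +13.5 | 0.10 |
| success letrozole, failure programmed | 51/74 | 27/74 | +32.4 | < 0.001 |

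With equal numbers missing, the two same-direction runs must give the same difference, because the same 7 is added to both numerators. Only the opposed runs show how far the missing women could move the result. This illustration puts the whole 10% loss before the scan and treats all 74 women per arm as the denominator.

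**The case against.** The strongest reply is that the damage is small. The LOCF figures above move the between-arm difference by less than 1 point at equal 10% missingness, and none of them alters the primary conclusion. That stands, and it sets the severity. Part of what LOCF would do is also sensible: a negative β-HCG carried forward gives not pregnant.

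Several stronger statements are tempting, and the document does not support them.
- A reader might infer that the protocol instructs the analyst to turn a positive β-HCG or scan into a later success. No mapping between stages is written. Conversion is what LOCF implies if it is applied across stages.
- A reader might infer that women lost before the β-HCG test drop out of the intention-to-treat set. The article does not say so. For them LOCF is undefined, or defaults to not pregnant.
- The range from +13.5 to +32.4 points might be read as the effect of LOCF. It is not: it shows the choice between worst/best scenarios.
- A reader might conclude that the planned sensitivity analysis cannot reveal fragility. Its wording is compatible with opposed arms, so that part is a request for clarification.

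It is also fair to say that counting a missing result as a failure is a single imputation that does not follow from MAR. It is proposed as an explicit, executable definition of success, with a separate MAR analysis beside it.

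Finally, an unseen analysis plan might hold more detail. But the article names the method, and for these outcomes the named method is unsuitable.

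**Conclusion.** The point holds in a limited form. LOCF is inconsistent with the stated MAR assumption, cannot be applied to birth weight, and for the staged pregnancy outcomes is either undefined or biased towards later success. At equal 10% missingness the bias in the difference is at most about 0.6 points for both live birth and clinical pregnancy, under the assumed loss rates. With no true effect it could reach 1.1 to 3.3 points for live birth if missingness were as unequal as 20% against 0%. Live birth and abortion carry most of the exposure.

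The undefined direction of the worst/best analysis is a separate matter and could weigh more. At the planning rates with 7 missing per arm, it separates P about 0.005 from P = 0.10. Actual losses before the scan may be smaller, because the 10% is a general follow-up figure and follow-up runs to 6 weeks after delivery.

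This should be fixed, but it does not by itself threaten the primary result.

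**What to change.** In the Data analysis section:
- Delete LOCF.
- For clinical pregnancy and live birth, count a woman in the analysis set with no documented success as not successful. Wording this by analysis set leaves the stated denominator (women who received a transfer) untouched; any change to it should be decided and stated separately.
- Add, as the sensitivity analysis under MAR, a simple multiple imputation from arm and a few baseline variables. With about 7 women missing per arm, a richer model would not be stable.
- State that the worst/best analysis is arm-opposed: letrozole worst with programmed best, and the reverse.
- Do not impute birth weight.

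Counting missing as not successful penalises the arm with more losses, so the number missing per arm should be reported beside it. The cost is a few sentences and a few extra sensitivity runs. The change should be made before outcomes are seen by arm; the article reports that enrolment was still running at submission.

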### Follow-up plan

There are four follow-up visits via medical records or telephone calls if women achieve clinical pregnancy.

Around 13 weeks of gestation, information on the ongoing pregnancy and any first-trimester pregnancy complications, such as early abortion and ectopic pregnancy, will be collected.

Around 29 weeks gestation, the second-trimester pregnancy complications—such as hypertensive disorders of pregnancy, gestational diabetes mellitus, and late abortion—will be recorded.

At the time of delivery, information on obstetrical and perinatal complications, as well as neonatal medical records, is acquired.

The final visit follows the postpartum complications and neonatal complications 6 weeks after delivery.

Timely follow-up visits should be conducted to reduce the number of participants who discontinue or deviate from intervention protocols.

Women will be asked about adverse events at each visit. Adverse events (AEs) are defined as any adverse medical problems that arise during the research period, without regard to their connection to the intervention. AEs in this study will be collected systemically and divided into study-related AEs and non-study-related AEs, which will be judged by clinicians at the time of recording every clinic visit.

All AEs will be recorded in detail and reported. Once any adverse reaction occurs during medication use, the drug will be stopped immediately. Serious AEs will be reported to the principal investigator immediately, and appropriate measures will be initiated instantly. The ethics committee will determine whether the AE is likely to have been associated with the experimental drug. The following conditions are considered serious AEs: death, life-threatening, severe or permanent disability, congenital malformation or birth defect, neonatal death within 6 weeks of delivery, or any other event that the local principal investigators deem serious. Adverse events must be timely noted and reported.

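### Missing outcomes are declared missing at random but filled by last observation carried forward, which that assumption does not justify and which is undefined for one-time pregnancy and birth outcomes

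*Protocol article*

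**What the plan says.** All of this is in the protocol article.

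- **Data analysis, missing data:** "Missing data will be treated as missing at random and will be imputed using the last observation carried forward method". The sentence is not limited to particular outcomes and does not say which value is carried. It is followed by a plan that "a sensitivity analysis will be done under the hypothesis of the worst and the best outcomes for each missing individual".
- **Data analysis, primary test:** "The primary analysis will be performed according to the intention-to-treat (ITT) principle", and "The primary outcome, clinical pregnancy rate, will be analysed using the chi-square test".
- **Outcome and outcome assessments:** one serum beta-hCG is taken two weeks after transfer; 10 IU/L or more defines biochemical pregnancy. Then: "Around 5 weeks following embryo transfer, a transvaginal ultrasound is carried out to confirm clinical pregnancy". Live birth counts deliveries from 28 weeks of gestation.
- **Follow-up plan:** clinically pregnant women have four contacts, at about 13 weeks, about 29 weeks, delivery and 6 weeks after delivery. Each contact collects different events. Hypertensive disorders and gestational diabetes, for example, belong to the second contact: "Around 29 weeks gestation, the second-trimester pregnancy complications".
- **Sample size:** 65% versus 40.8%, 66 women per group, 80% power, alpha 0.05. "Considering a 10% follow-up drop-out rate, our target sample size will be 148 women".

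**The concern.** The sentence joins an assumption to a method that does not follow from it. Missing at random says that, given the observed data, missingness does not depend on the unseen value. LOCF needs something else: that the outcome stays at its last recorded value. It also enters the filled value into the chi-square test as if it had been observed, so imputation uncertainty is ignored.

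LOCF further presupposes repeated measurements of one variable, and none of the named outcomes has them. Anyone applying the rule must borrow a different state or give up. Two analysts could code the same lost woman in opposite ways and both comply. In an open-label trial the losses may differ by arm, and a single-value fill turns a difference in loss into a difference in outcome rates.

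**Working it through.** **1. What could be carried forward, outcome by outcome**

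| Outcome | When it is known | Last earlier state | Effect of carrying it |
|---|---|---|---|
| Clinical pregnancy | scan about 5 weeks after transfer | beta-hCG at 2 weeks, or the pre-transfer state | positive test: biochemical losses and ectopics count as clinical pregnancies; pre-transfer state: every lost woman counts as not pregnant |
| Live birth | delivery | ongoing pregnancy | not a birth outcome, or an assumed live birth |
| Hypertensive disorders, gestational diabetes | about 29 weeks | none so far | counts as complication-free |
| Birth weight | delivery | none | rule cannot be applied |

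**2. The plan's own figure**

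Two-sided 5%, 80% power, pooled variance, no continuity correction; mean rate (0.65 + 0.408)/2 = 0.529:

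n = [1.96·√(2·0.529·0.471) + 0.8416·√(0.65·0.35 + 0.408·0.592)]² / 0.242² = 65.6, so 66 per arm. Then 66/0.9 = 73.3, so 74 per arm and 148 in total. This reproduces the plan.

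The power and error rates below come from exact binomial enumeration of the uncorrected chi-square test. All women in each arm are taken as counted in the denominator.

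**3. Reading A: every lost woman is filled as not pregnant**

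Recorded rate = true rate × (1 − loss).

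- 10% loss in each arm: 0.65 × 0.9 = 58.5% and 0.408 × 0.9 = 36.7%. The difference is 21.8 points instead of 24.2.
- Power at 74 per arm: 78.3%. For comparison, 66 per arm with complete data gives 79.2%, and 74 with complete data gives 86.1%.
- No true effect, loss 5% versus 15% (my assumption): the spurious difference is 0.10 × the true rate, which is 4.1 points at 40.8% and 6.5 points at 65%. Rejection rates are 8.2% (true rate 40.8%), 11.1% (52.9%) and 13.5% (65%).
- The same with 3% versus 7% (also assumed): 5.7% to 6.7%.
- Reference with no loss: 5.0% to 5.8%.

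**4. Reading B: the beta-hCG result is carried forward**

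Assume that a share f of positives never becomes a clinical pregnancy, with f = 10% to 20%, and that the test result is known for lost women. The positive rate is p/(1 − f), so with loss d the overcount is d × [p/(1 − f) − p].

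- Letrozole arm, d = 10%: 0.1 × (0.722 − 0.65) = 0.7 points, up to 0.1 × (0.8125 − 0.65) = 1.6 points.
- Programmed arm, d = 10%: 0.1 × (0.453 − 0.408) = 0.5 points, up to 0.1 × (0.51 − 0.408) = 1.0 point.
- The difference between arms moves by 0.3 to 0.6 points.
- No true effect, loss 5% versus 15%: rejection rate 5.1% to 6.1%, against 5.0% to 5.8% with no loss.

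**5. The planned worst/best analysis at 10% loss per arm**

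- Worst for letrozole: 58.5% versus 0.408 × 0.9 + 0.1 = 46.7%, a difference of 11.8 points.
- Best for letrozole: 0.65 × 0.9 + 0.1 = 68.5% versus 36.7%, a difference of 31.8 points.

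**The case against.** The strongest reply is that the damage to the primary outcome may be slight, and much of that stands.

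- A woman with a beta-hCG below 10 IU/L is in practice a known non-pregnancy, so carrying that result forward is right. Only test-positive women who miss the scan, and women with no test, are truly in doubt.
- The 10% in the sample size section is a follow-up drop-out rate. The article does not say that 10% will miss the 5-week scan, so for the primary outcome it is best read as an upper bound.
- Even under Reading A with equal loss, power is about one point below that of 66 complete women per arm. The drop from 86.1% compares with a trial that loses nobody, which was not planned.
- The article plans retention measures, allows follow-up through medical records, and adds best- and worst-outcome runs.

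Three stronger inferences are tempting but unsupported. A reader might conclude that the plan codes lost women as not pregnant; the article does not say what is carried, so every coding above is a possible reading only. A reader might take the 10% to 20% of positives that never become clinical as the overcount in an arm's rate; it applies only to lost, test-positive women. A reader might see a conflict between enlarging the sample for drop-out and then filling the missing outcomes; the two are compatible, and multiple imputation would also keep all 148 women.

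What the reply does not rescue is the rule itself. The sensitivity runs span 11.8 to 31.8 points at 10% loss per arm, which bounds the answer but supplies no valid main estimate. Nor is this detail left to an unseen analysis plan, because the method is stated.

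**Conclusion.** The rule is wrong as written. LOCF does not follow from missing at random, treats filled values as observed, and has no defined meaning for the trial's one-time outcomes.

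The consequence is probably largest for live birth and complications, where contact must last to delivery and 6 weeks afterwards and where the borrowed state is an unfinished pregnancy or an absence of events so far. This is a judgement from the follow-up schedule; the article gives no loss rates by outcome.

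For clinical pregnancy the effect runs from nearly nothing (Reading B) to a 2.4-point shrinkage of the planned difference under equal 10% loss (Reading A). The raised false-positive rates of 8.2% to 13.5% need both Reading A and a 5%/15% loss split that appears nowhere in the document, so they illustrate what the rule permits and do not forecast what will happen.

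**What to change.** In the Data analysis section, delete LOCF and state:

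1. A beta-hCG below 10 IU/L two weeks after transfer is a known absence of clinical pregnancy and is not imputed.
2. Binary outcomes that are truly unknown are handled by a method valid under missing at random. One example is multiple imputation with a small prespecified model that includes arm and last known pregnancy status, pooled with Rubin's rules. The model should stay small: 10% of 74 is about 7 women per arm, too few to support separate models by arm with six centres and several covariates.
3. Birth weight is analysed in infants with a recorded weight.
4. The worst- and best-outcome runs stay as sensitivity analyses.

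The cost is one paragraph, a little more analysis work and slightly wider intervals. Sample size and data collection do not change. Enrolment was still under way when the article was written; the change should be made before results by arm are seen.
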